### Sample size and power

We assume a true sham responder rate of 0.22 or less, and a treatment responder rate of 0.68 or higher, based upon pilot study observations and assuming 10% attrition of participants during the study. Thus, a sample size of 60 will support 80% power to distinguish between the arms, in a two-sided exact test at the 0.05 significance level. Considering the heterogeneity of prospective participants, proposed sample size of 60 participants (30 per arm) will ensure 80% power for primary endpoint comparison, allowing for precise estimation of responder rates in different demographic subpopulations. Assuming 25% attrition rate of participants in screening based on pilot study, the required number of participants to be screened is 80. The proposed sample size is consistent with other similar studies (NCT05020834, NCT04725019, NCT05154253, NCT05351138).

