## Proposed solution

To address this need, SpineX Inc. has developed a noninvasive spinal neuromodulation device SCiP™ (Spinal Cord Innovation in Pediatrics), a Class II, Nonsignificant Risk Device, recognized with a breakthrough device designation by US FDA for treating the underlying condition associated with CP. SCiP™ directly modulates the spinal cord neural circuits and indirectly the supraspinal neural circuits by transcutaneously delivering novel electrical pulses below motor thresholds to neuromodulate spinal and supraspinal networks into an activated state of plasticity. Although the exact mechanisms by which transcutaneous electrical spinal neuromodulation transforms the spinal neural networks into more functional states is not fully understood, considerable insights have been gained from studies of spinal cord injury and other forms of paralysis (Edgerton et al., 2021). Our initial findings demonstrated that acute (single session) neuromodulation with SCiP™ in children with CP significantly improved the postural and locomotor abilities in 11 out of the 12 participants (Gad et al., 2021).

In the chronic approach, we combined neuromodulatory (SCiP™) and rehabilitative (ABNT) strategies (Hastings et al., 2022). In our pilot trial, 16/16 children (age 2.5–16) who received SCiP™ therapy in conjunction with ABNT for 8 weeks, demonstrated significant motor recovery. Their Gross Motor Function Measure-88 (GMFM88) scores improved by 13.3 ± 1.3 points (*p* < 0.05), more than twice the minimal clinically important differences (MCID) of 5 points (Storm et al., 2020), and greater than other available treatment options. Functional improvements persisted even in the absence of active stimulation, supporting our working hypothesis that spinal neuromodulation facilitates targeted spinal-supraspinal neural plasticity needed for long-term recovery.

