### Study population and recruitment

Up to 80 participants (ages ≥2 and ≤ 13 years), diagnosed with CP, spastic diplegia, spastic hemiplegia or spastic quadriplegia, and GMFCS Level I-V will be consented to achieve a minimum of 60 evaluable datasets (30 treatment, 30 control) at the primary Phase I endpoint of 8 weeks (see statistical analysis for sample size calculation). The inclusion/exclusion criteria are described in Supplementary Table S1.

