### Statistical analysis

Randomization will be stratified by age and GMFCS level. Demographics and baseline characteristics will be summarized for all patients using summary statistics for continuous variables (number of patients, mean, standard deviation, median, minimum and maximum) and using group frequencies or percentages for discrete variables. Study arms will be compared with respect to these characteristics using two-sample t-tests, binomial-based tests, chi-squared tests, or nonparametric alternatives. The primary endpoint, the GMFM88 score responder rate (i.e., >5-point increase from baseline), will be estimated and compared between groups using a two-sided chi-squared test at the 0.05 significance level. In the event of small expected cell sizes (e.g., <5), an exact test will be used. If baseline characteristics differ between study arms, logistic regression will be employed, with those characteristics, as well as stratification factors, as covariates. The secondary endpoint, the Modified Ashworth Scale (MAS) responder rate (i.e., > 0.45 change from baseline), will also be estimated and compared between treatment arms using a two-sided chi-squared test. Change-from-baseline to Phase I evaluation in MAS, GMFM88 Dimension A, B, C, D, and E, PEDI-CAT, and 10MWT (GMFCS levels I, II, and III only) will be computed for each participant as the difference between the two measurements; these will be compared between treatment groups using two-sided, two-sample *t*-tests at the 0.05 significance level. Data transformations or nonparametric methods will be substituted if the data are not found to be normally distributed. As an additional ancillary analysis, the Phase I primary, secondary, and ancillary efficacy endpoints will be compared between study arms using logistic regression, analysis of variance, or other statistical modeling appropriate to the endpoint, with stratification factors and other baseline and demographic factors as covariates. Interaction testing and subgroup analyses will be employed to investigate consistency or heterogeneity of treatment effect across subgroups based upon age, gender, race, ethnicity, clinical site, underlying condition, and/or other baseline and demographic factors. The ancillary endpoints will also be estimated in the treatment group as change from baseline to the final evaluation visit (post 8-or 16-week, visit 34), and in the control group as change from the Phase I post 8-week evaluation to the final evaluation visit (post 8 or 16-week, visit 34), with 95% confidence intervals (CI). Similar methods will be employed to characterize change from baseline (as well as change from final evaluation visit) through the follow-up phase (week 24). Safety analyses will establish frequencies of adverse events, in total and by type, along with 90% CIs. Analyses will be conducted under intent-to-treat principles. The extent of missing data will be evaluated and addressed using multiple imputation (subject to evidence supporting an assumption of Missing at Random) together with sensitivity analyses.

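### The stated 80% power and the minimum of 60 evaluable children do not follow from the plan's own responder rates and attrition figures; the power error is conservative

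*Protocol article*

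**What the plan says.** Under Sample size and power, the Protocol article sets the two rates as bounds: "We assume a true sham responder rate of 0.22 or less" and "a treatment responder rate of 0.68 or higher". It adds 10% attrition during the study and concludes that "a sample size of 60 will support 80% power to distinguish between the arms, in a two-sided exact test at the 0.05 significance level". It repeats the 80% for 60 participants, 30 per arm, and describes this number as "allowing for precise estimation of responder rates in different demographic subpopulations".

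On enrolment, the same section says: "Assuming 25% attrition rate of participants in screening based on pilot study, the required number of participants to be screened is 80". Study population and recruitment says that up to 80 children "will be consented to achieve a minimum of 60 evaluable datasets (30 treatment, 30 control") at the 8-week primary endpoint. The Abstract describes sixty participants recruited and divided equally between two groups.

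Under Statistical analysis, the primary responder rate is to be "compared between groups using a two-sided chi-squared test" at the 0.05 level, with an exact test where expected cell sizes are small.

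**The concern.** Two stated figures look inconsistent with the inputs printed beside them.

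The first is the power. A difference of 46 percentage points (0.68 less 0.22) is large for 30 per arm, and 80% looks too low for it. If so, at least one of the rates, the sample size and the power is misreported, and a reader cannot tell which. A bare 80% also hides how much margin the design has and at what sham rate that margin runs out.

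The second is the flow of participants. Two losses are assumed, one in screening and one during the study, but the step from 80 to 60 appears to use only the first. The article then promises 60 as the number evaluable at week 8, when 60 is the number left to randomise.

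**Working it through.** **Inputs** (Sample size and power, unless noted): sham rate 0.22; treated rate 0.68; two-sided alpha 0.05; 60 children, 30 per arm; attrition during the study 10%; screening loss 25%; 80 screened. From Study population and recruitment: up to 80 consented, at least 60 evaluable at week 8. From Statistical analysis: chi-squared test, exact test if expected cells are small (5 is the article's example).

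**Step 1. Attempt to reproduce 80%.** Power is the sum over all x and y of Bin(x; n, 0.22) × Bin(y; n, 0.68), counting only the tables for which the test gives p ≤ 0.05. After 10% attrition, n per arm is 30 × 0.90 = 27.

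| Method | 30 per arm | 27 per arm |
|---|---|---|
| Fisher exact, two-sided | 93.7% | 89.5% |
| Chi-squared, Fisher if an expected cell is below 5 | 96.4% | 93.7% |
| Normal approximation | 96.6% | 94.8% |

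Counting dropouts as non-responders at 30 per arm gives 87.7% with the exact test (rates 0.22 × 0.9 = 0.198 and 0.68 × 0.9 = 0.612), or 82.9% if only the treated rate is reduced. None of these gives 80% at the stated alpha.

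**Step 2. What 80% would correspond to.**
- Sample size at the stated rates, exact test: 21 per arm gives 78.4% and 22 per arm gives 81.9%. So 22 per arm, or 44 evaluable; 44 / 0.90 = 48.9, about 49 randomised.
- Treated rate with sham at 0.22, exact test: at 30 per arm, 0.60 gives 80.3%. At 27 per arm, 0.62 gives 78.9% and 0.63 gives 81.0%.

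**Step 3. Participant flow.**
- 80 × (1 − 0.25) = 60 randomised.
- 60 × (1 − 0.10) = 54 evaluable, if all of the 10% falls by week 8.
- In reverse: 60 / 0.90 = 66.7, so 67 randomised; 66.7 / 0.75 = 88.9, so 89 consented (90 if 67 is rounded up first).

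Because 60 / 0.75 is exactly 80, the ceiling of 80 covers the screening loss and nothing else.

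**Step 4. Sensitivity to the sham rate**, treated rate 0.68, planned chi-squared rule:

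| Sham rate | 30 per arm | 27 per arm |
|---|---|---|
| 0.22 | 96.4% | 93.7% |
| 0.30 | 86% | 79.7% |
| 0.35 | 75% | 67% |

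**Step 5. Subgroup precision.** Half of an arm is 15 children. At a rate of 0.68 the 95% half-width is 1.96 × √(0.68 × 0.32 / 15) = 0.236, about ±24 percentage points.

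**The case against.** The rates are given as bounds, and the text says that 60 will support or ensure 80% power. Read as a floor, that is true: at 0.22 and 0.68 the power exceeds 80% even with 54 children. This stands, and it rules out the inference that the primary comparison is underpowered. What remains is that the article presents 60 as the result of those inputs, and it is not.

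The 10% attrition is for the whole study, which runs to about 30 weeks with an optional extension and a follow-up. Part of it may fall after week 8, and multiple imputation may keep randomised children with missing data in the comparison. This also stands: 54 is the low end and not a forecast. But imputation does not turn a missing assessment into an evaluable dataset, and with exactly 60 randomised a single early loss breaks the minimum.

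A reader might infer two further faults that the documents do not support:
- **That powering on an exact test contradicts the chi-squared analysis.** The analysis keeps an exact test as its fallback, and powering on the more conservative test is acceptable. The difference also moves power further from 80%, so it does not explain the figure.
- **That the sham rate has no basis.** In the 8-week pilot summarised under Proposed solution, all 16 children were ones "who received SCiP™ therapy in conjunction with ABNT for 8 weeks, demonstrated significant motor recovery", and no sham arm is described. But that is a short summary, and the article cites several pilot studies. It does not show where 0.22 comes from; this does not establish that no source exists.

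**Conclusion.** The point holds on two counts.

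1. At the stated rates and alpha, 60 children give about 90% to 94% power with the exact test, or 94% to 96% under the planned chi-squared rule. The lower figure in each range assumes the full 10% loss. The stated 80% is 10 to 14 points below the exact-test figures and cannot be traced to its inputs. The error is in the safe direction as long as the assumed rates hold.
2. Eighty consented yields 60 randomised, so the minimum of 60 evaluable at week 8 has no allowance for loss. The expected number lies between 54 (all of the 10% lost by week 8) and 60 (none lost).

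The margin depends on the sham rate. With 27 per arm and the planned test, power is about 80% at a sham rate of 0.30 and 67% at 0.35. The claim of precise subgroup responder rates is also not supported by about 15 children per arm.

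These are figures to correct in the text. They do not put the primary comparison at risk under the plan's own assumptions.

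**What to change.** - Restate the sample size as 60 randomised, with about 54 to 60 evaluable at week 8, and replace the minimum of 60 evaluable datasets with those figures. If 60 evaluable is a firm requirement, the alternative is about 67 randomised and a consent ceiling of 89 to 90.
- Replace the 80% with the power that follows: about 90% to 94% (exact) or 94% to 96% (chi-squared rule). Or keep 80% and state the rates it belongs to with the exact test: about 0.60 treated at 30 per arm, or about 0.63 at 27 per arm, against sham 0.22.
- Add a short sensitivity range for the sham rate on the planned test (27 per arm: about 80% at 0.30, 67% at 0.35), and state where the 0.22 comes from.
- Drop the claim of precise estimation in subpopulations.

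Apart from the alternative of a higher consent ceiling, these are text changes and need no additional children. Trial objectives says that the sample size was aligned with the FDA, so a changed evaluable target should be put to the agency.

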### Randomization and blinding

Participants will be randomized into a treatment (SCiP™) arm and control (sham) arm in a 1:1 ratio. A block randomization technique will be employed, and randomization will be stratified by age (2–7 and 8–13) and GMFCS level (levels stratified as I + II + III & IV + V; ambulatory and non-ambulatory groups). All participants and the clinicians administering the assessment will be blinded to the initial group assignment. The sham device will be physically identical and intensity on the LCD display will be shielded from the participants. At Phase I primary evaluations, participants will be asked what treatment they believe they received using the Bang blinding index (Bang et al., 2004). Participants will not be blinded during the Phase II, open label extension during which all subjects will receive SCiP™ treatment.

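### Sixty children do not allow precise responder-rate estimates in demographic subgroups: at the protocol's own rates, a half-sample subgroup has 95% intervals about 40 to 50 points wide

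*Protocol article*

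**What the plan says.** The Sample size and power section sets its assumptions as follows. For the control arm: "We assume a true sham responder rate of 0.22 or less". For the SCiP arm it takes "a treatment responder rate of 0.68 or higher". Losses enter by "assuming 10% attrition of participants during the study". It concludes that "a sample size of 60 will support 80% power to distinguish between the arms, in a two-sided exact test at the 0.05 significance level". The next sentence restates this, saying that the "proposed sample size of 60 participants (30 per arm) will ensure 80% power for primary endpoint comparison". The same sentence then credits the design with a second property, namely "allowing for precise estimation of responder rates in different demographic subpopulations". It gives no interval width, no subgroup size and no definition of precision.

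The Statistical analysis section then plans the subgroup work: "Interaction testing and subgroup analyses will be employed to investigate consistency or heterogeneity of treatment effect across subgroups based upon age, gender, race, ethnicity". Its list of factors also includes the study site, the underlying condition and an open-ended reference to further baseline factors. The primary test is fixed separately as the overall comparison of responder rates between arms.

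**The concern.** Power to detect a large overall difference and precision of a rate within a subgroup are different properties, and the first does not produce the second. With 30 per arm and an assumed difference of 46 points (0.68 − 0.22), the overall test can have ample power while every subgroup rate remains poorly determined.

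The clause forms part of the justification for the sample size, so a reader of the eventual results may lean on it when responder rates are shown by age, gender, race or ethnicity. Two misreadings follow easily. A subgroup rate may be taken as well established when its interval covers half the scale. A non-significant interaction may be taken as evidence that the effect is consistent when the test had little chance of showing otherwise.

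**Working it through.** **Inputs.** Responder rates 0.68 and 0.22, 30 per arm, two-sided 0.05, exact test and 10% attrition come from Sample size and power. The 1:1 allocation comes from Randomization and blinding. Subgroup sizes are my assumption: an equal split into two gives 30/2 = 15 per arm, and an equal split into four gives 30/4, about 8 per arm.

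**The plan's own figure first.** Fisher's exact test, enumerated over both binomial distributions at 0.22 and 0.68, has power 93.7% with 30 per arm and 89.5% with 27 per arm (30 × 0.9). The stated 80% is not reproduced, because the sample is larger than 80% requires: 22 per arm already gives 81.9%. The overall comparison is therefore not underpowered at these rates.

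**Precision of one responder rate.** Three 95% intervals:

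- Wald: p ± 1.96 × √[p(1 − p)/n].
- Wilson: half-width z√[p(1 − p)/n + z²/(4n²)] / (1 + z²/n), with z = 1.96.
- Exact (Clopper-Pearson), at the whole count nearest to n × p.

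Example, SCiP with n = 15: 1.96 × √(0.68 × 0.32/15) = 1.96 × 0.1204 = 0.236, a full width of 47 points. For sham: 1.96 × √(0.22 × 0.78/15) = 1.96 × 0.1070 = 0.210, a full width of 42 points.

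| Per arm | Arm | Wald width | Wilson width | Exact interval (width) |
|---|---|---|---|---|
| 30 (whole arm) | SCiP | 33 | 32 | 20/30: 47% to 83% (36) |
| 30 (whole arm) | Sham | 30 | 29 | 7/30: 10% to 42% (32) |
| 15 (half sample) | SCiP | 47 | 43 | 10/15: 38% to 88% (50) |
| 15 (half sample) | Sham | 42 | 39 | 3/15: 4% to 48% (44) |
| 8 (quarter sample) | SCiP | 65 | 54 | 5/8: 24% to 91% (67) |
| 8 (quarter sample) | Sham | 57 | 51 | 2/8: 3% to 65% (62) |

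Widths are in percentage points. If 10% attrition comes off the 30, a half-sample subgroup has 13 to 14 per arm. The exact widths become 50 to 52 points (SCiP) and 46 to 49 (sham).

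**Precision of the between-arm difference, 15 per arm.** 1.96 × √[(0.68 × 0.32 + 0.22 × 0.78)/15] = 1.96 × √(0.3892/15) = 1.96 × 0.1611 = 0.316, or about ±32 points around 46.

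**What a tighter estimate would need.** For ±10 points at 0.68: n = 1.96² × 0.68 × 0.32/0.10² ≈ 84 children in one arm of one subgroup, more than the whole trial.

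**Power inside a subgroup.** Fisher power for the full 0.22 versus 0.68 contrast with 15 per arm is 58%.

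**Power of an interaction test** (risk-difference scale, two equal subgroups, 15 per arm in each, two-sided 0.05 assumed because the section states no level for these tests):

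- Full effect in one subgroup, none in the other (0.22 in both arms): SE = √[(0.3892 + 2 × 0.1716)/15] = 0.221; 0.46/0.221 = 2.08; power about 55%.
- Full effect in one, half in the other (0.45 versus 0.22): SE = √[(0.3892 + 0.2475 + 0.1716)/15] = 0.232; 0.23/0.232 = 0.99; power about 17%.

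**The case against.** The strongest reply is that this is one clause of rationale. No sample size, test, endpoint or success rule rests on it, and the primary comparison is well powered. That is correct, and it keeps the point to a correction of wording. It does not make the clause true. The clause asserts a property of the design, and no statistical analysis plan can make 15 children per arm precise.

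A second reply is that the documents give no subgroup sizes, so the half-sample split is mine. It is, but the whole-arm row of the table needs no such assumption: at these rates even 30 children give a width of 29 to 36 points, and a subgroup has fewer. An unequal split makes the smaller subgroup worse than shown.

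A third concerns attrition. Study population and recruitment aims for at least 60 evaluable children at the Phase I endpoint, so 30 per arm may already be net of losses. The main figures therefore use 30, and the attrition figures are only a sensitivity check.

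Several stronger readings are tempting and are not supported:

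- A reader might infer that the Statistical analysis section is at fault for naming no primary subgroup and not calling the analyses exploratory. That is commonly left to the analysis plan, which is not shown. The section describes the work as investigative and makes no confirmatory subgroup claim.
- A reader might infer that an effective and an ineffective subgroup could never be distinguished. Interaction power of about 55% in that extreme case is weak, but it is not zero.
- A reader might apply the clause to clinical sites, with very few children each. Site is not a demographic subpopulation, so it does not test this statement.
- A reader might compute a 26% chance of at least one false interaction (1 − 0.95⁶). That assumes six independent tests at 0.05, and it is not the probability that an observed difference is due to chance.

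**Conclusion.** The clause is wrong as written. At the protocol's own rates, and assuming an equal split into two subgroups, a responder rate carries a 95% interval about 40 to 50 points wide and a between-arm difference about ±32 points. The 50-point figure belongs to the exact interval for SCiP only; the sham intervals are narrower. The conclusion does not depend on the interval method, and finer subgroups or attrition make it worse.

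The finding is limited to the stated precision and what may be read from it. It does not show that the trial is too small for its primary endpoint, that the planned subgroup analyses are improper, or that they should be confined to particular factors.

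**What to change.** In Sample size and power, delete the clause on subpopulations, or replace it with the attainable precision. For a subgroup of half the sample (15 per arm), this is roughly ±24 points for a SCiP responder rate and ±32 points for the between-arm difference (95% Wald, at 0.68 and 0.22).

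Add one sentence, there or in Statistical analysis, saying that subgroup responder rates and interaction tests are descriptive and that a non-significant interaction is not evidence of a consistent effect.

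No change to sample size, design or data collection is needed. The only cost is a less favourable stated property of the design.

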### Statistical analysis

Randomization will be stratified by age and GMFCS level. Demographics and baseline characteristics will be summarized for all patients using summary statistics for continuous variables (number of patients, mean, standard deviation, median, minimum and maximum) and using group frequencies or percentages for discrete variables. Study arms will be compared with respect to these characteristics using two-sample t-tests, binomial-based tests, chi-squared tests, or nonparametric alternatives. The primary endpoint, the GMFM88 score responder rate (i.e., >5-point increase from baseline), will be estimated and compared between groups using a two-sided chi-squared test at the 0.05 significance level. In the event of small expected cell sizes (e.g., <5), an exact test will be used. If baseline characteristics differ between study arms, logistic regression will be employed, with those characteristics, as well as stratification factors, as covariates. The secondary endpoint, the Modified Ashworth Scale (MAS) responder rate (i.e., > 0.45 change from baseline), will also be estimated and compared between treatment arms using a two-sided chi-squared test. Change-from-baseline to Phase I evaluation in MAS, GMFM88 Dimension A, B, C, D, and E, PEDI-CAT, and 10MWT (GMFCS levels I, II, and III only) will be computed for each participant as the difference between the two measurements; these will be compared between treatment groups using two-sided, two-sample *t*-tests at the 0.05 significance level. Data transformations or nonparametric methods will be substituted if the data are not found to be normally distributed. As an additional ancillary analysis, the Phase I primary, secondary, and ancillary efficacy endpoints will be compared between study arms using logistic regression, analysis of variance, or other statistical modeling appropriate to the endpoint, with stratification factors and other baseline and demographic factors as covariates. Interaction testing and subgroup analyses will be employed to investigate consistency or heterogeneity of treatment effect across subgroups based upon age, gender, race, ethnicity, clinical site, underlying condition, and/or other baseline and demographic factors. The ancillary endpoints will also be estimated in the treatment group as change from baseline to the final evaluation visit (post 8-or 16-week, visit 34), and in the control group as change from the Phase I post 8-week evaluation to the final evaluation visit (post 8 or 16-week, visit 34), with 95% confidence intervals (CI). Similar methods will be employed to characterize change from baseline (as well as change from final evaluation visit) through the follow-up phase (week 24). Safety analyses will establish frequencies of adverse events, in total and by type, along with 90% CIs. Analyses will be conducted under intent-to-treat principles. The extent of missing data will be evaluated and addressed using multiple imputation (subject to evidence supporting an assumption of Missing at Random) together with sensitivity analyses.

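### The primary test omits the randomisation strata, and a logistic model triggered by chance baseline differences leaves unclear which result is primary

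*Protocol article*

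**What the plan says.** Under Randomization and blinding, the protocol article states that "randomization will be stratified by age (2–7 and 8–13) and GMFCS level", with GMFCS grouped as I to III and IV to V. That makes four strata, allocated 1:1.

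Under Statistical analysis, four statements bear on the primary endpoint:

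- The GMFM88 responder rate "will be estimated and compared between groups using a two-sided chi-squared test at the 0.05 significance level". No stratification term is mentioned.
- The only stated fallback for that test is for sparse data: "In the event of small expected cell sizes (e.g., <5), an exact test will be used".
- Baseline characteristics are tested between arms: "Study arms will be compared with respect to these characteristics using two-sample t-tests, binomial-based tests, chi-squared tests, or nonparametric alternatives".
- A conditional rule follows: "If baseline characteristics differ between study arms, logistic regression will be employed, with those characteristics, as well as stratification factors, as covariates".

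The section later describes a separate ancillary analysis of the Phase I endpoints, the primary one included, by regression with stratification and other baseline factors as covariates. It gives no criterion for deciding that a characteristic differs and no list of candidate characteristics. It also gives no ranking of the chi-squared result against the triggered logistic result.

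**The concern.** There are two linked problems.

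First, the default test does not use the factors on which the trial was balanced by design. Stratified randomisation removes between-stratum variation from the comparison of arms. A crude test still charges for that variation, so it is conservative whenever the strata predict response.

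Second, the conditional rule lets observed baseline data decide whether a logistic model is fitted and what goes into it. Under randomisation an observed imbalance is a chance event, so a test of it says nothing about whether adjustment is needed. Because the ranking of the two results is not stated, a triggered rule leaves two candidate primary results. They also estimate different things: a contrast of crude responder rates, or an odds ratio conditional on covariates chosen from the data. The article writes this rule down for the primary endpoint, so an analysis plan that followed the article would carry it forward.

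**Working it through.** **Inputs from the protocol article (Sample size and power).** "We assume a true sham responder rate of 0.22 or less, and a treatment responder rate of 0.68 or higher"; 60 participants, 30 per arm; "assuming 10% attrition of participants during the study", which gives 60 × 0.9 = 54 evaluable, 27 per arm. Stated power is 80% for a two-sided exact test at 0.05.

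**Assumptions, because the article gives no figures.** Responder rates by stratum, stratum sizes, the number of baseline characteristics, and the threshold for calling them different.

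**1. The plan's own power figure.** Exact enumeration at 0.22 versus 0.68 gives:
- Fisher: 89.5% at 27 per arm, 93.7% at 30 per arm.
- Pearson chi-squared: 93.7% at 27 per arm, 96.4% at 30 per arm.

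The stated 80% is not reproduced; it is on the low side, so the design has room to spare at its planned effect. Expected cells at 27 per arm are 27 × 0.45 = 12.15 responders and 27 × 0.55 = 14.85 non-responders. The chi-squared test, not the exact fallback, would therefore apply.

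**2. Crude against stratified test.** With n per arm, the crude statistic is z = (p1 − p0) / √(2p̄(1 − p̄)/n). With n_k per arm, m_k responders in total and a_k treated responders in stratum k, the Cochran-Mantel-Haenszel (CMH) statistic is z = Σ(a_k − m_k/2) / √ΣV_k, where V_k = n_k² m_k(2n_k − m_k) / [(2n_k)²(2n_k − 1)]. When arms are balanced within strata, the numerator is half the crude difference in responder counts. The two tests then differ only in variance.

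Simulation used a common odds ratio, no continuity correction, and assumed sham rates of 0.45/0.30/0.10/0.05. Strata were 8/8/7/7 per arm (7/7/7/6 in the row with 27 per arm). The mean sham rate with 30 per arm is (8 × 0.45 + 8 × 0.30 + 7 × 0.10 + 7 × 0.05)/30 = 0.235, close to the planned 0.22.

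| Odds ratio | Implied treatment rate | Per arm | Chi-squared | CMH |
|---|---|---|---|---|
| 1 (size) | 0.235 | 30 | 3.4% | about 5% |
| 11.4 | 0.68 (planned) | 30 | 96.7% | 97.9% |
| 11.4 | 0.68 (planned) | 27 | 94% | 96.9% |
| 6 | 0.56 | 30 | 77% | 84% |
| 4 | 0.49 | 30 | 52% | 62% |

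With a sham rate of 0.22 in every stratum and an odds ratio of 6, both tests have about 91% power, so nothing is lost.

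**3. How often the trigger fires by chance.** With k independent characteristics tested at 0.05, the probability of at least one difference is 1 − 0.95^k: 23% for k = 5, 34% for k = 8, 40% for k = 10, 54% for k = 15.

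**4. The rule followed mechanically.** This simulation used 2,000 trials per scenario, four strata, permuted blocks of 4, and eight further covariates each tested at 0.05. Power at 0.22 versus 0.68 with 54 evaluable:
- Strata not prognostic: switching rule 92.2%, CMH 92.8%.
- Each stratification factor with log-odds 2: switching rule 94.4%, CMH 99.0%, the largest gap seen.

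Across the null scenarios (54 and 60 evaluable), the rule's size was 2.6% to 5.4%. Taking the smaller of the two p-values gave at most about 6%.

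**5. Change of estimand.** In the planned-effect row, the conditional odds ratio is 11.4. The crude odds ratio from the same rates is (0.68/0.32)/(0.235/0.765) = 2.125/0.307 = 6.9. The two candidate results are not interchangeable. Only about 30 × 0.22 + 30 × 0.68 = 27 responders are expected, so few covariates can be supported.

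**The case against.** The strongest defence is that the article does name one primary test, with its level and a small-cell fallback, and that the logistic sentence never says it replaces that test. It can be read as supportive. That stands in part: the text is ambiguous, and a reader who infers an established switch of the primary analysis goes further than it allows. The opposite reading stays open because the covariate-adjusted ancillary analysis is described separately afterwards.

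A reader might also infer that the trial is underpowered because of this test. The figures do not support that. Losses of 6 to 10 points arise only at treatment rates of 0.49 to 0.56, below the planned 0.68. They also rest on an assumed nine-fold spread in sham rates. The Background describes heterogeneity of functional ability by GMFCS level and greater plasticity at younger ages, but gives no responder rate by stratum.

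Nor does the material support a claim of inflated false positives. The crude test is valid and errs on the safe side, and the switching rule stays at or near nominal size when followed mechanically.

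Finally, thresholds and covariate lists are commonly left to an analysis plan, and their absence is not the point here. The point is the affirmative rule that ties the primary-endpoint model to observed imbalance, and a default test that leaves out the design strata.

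**Conclusion.** The point holds as a matter of pre-specification, with efficiency second. The default primary test omits the four randomisation strata, and the article leaves open which result is primary when chance imbalance triggers the logistic model. The trigger would fire in roughly 23% to 54% of trials if 5 to 15 independent characteristics were tested at 0.05; both the number and the threshold are assumptions.

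The cost in power is nil if the strata are not prognostic. If they are as strong as assumed, it is about 1 to 3 points near the planned rates and about 6 to 10 points at the smaller effects examined. The switching rule itself loses up to about 5 points against a stratified test at the planned effect. This should be fixed, but it threatens neither the validity of the test nor the planned power.

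**What to change.** Before unblinding, make these changes:

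- Name one primary analysis: a Cochran-Mantel-Haenszel test over the four strata (age 2–7 or 8–13, by GMFCS I–III or IV–V), reported with a Mantel-Haenszel risk difference and 95% confidence interval.
- Make any small-cell fallback a stratified exact test, so that it addresses the same comparison.
- Delete the rule that triggers logistic regression when baseline characteristics differ. Baseline tables can stay descriptive.
- Keep one logistic model, with its covariates named in advance, as a sensitivity analysis only. With about 27 responders expected, the list should be short.

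The cost is wording. The strata are already recorded for randomisation, no further data or participants are needed, and essentially no power is lost if the strata prove not to be prognostic.
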